| Change in HIV RNA (log10) from baseline | Continuous: compare in DAART and SAT at 4 time points (3, 6, 12, and 18 months) | Intent-to-treat, missing values excluded | ANOVA for each time point and linear regression with GEE for overall comparison |
| **CD4 cell recovery** | | | |
| Change in CD4 cell count from baseline | Continuous: compare in DAART and SAT during active intervention (3, 6, and 12 months) | Intent-to-treat | ANOVA for each time point and linear regression with GEE for overall comparison |
| CD4 cell count | Continuous | Intent-to-treat | Linear regression with GEE & adjusting for initial CD4 at baseline |
| **Antiretroviral therapy use** | | | |
| Retention to ART | Time to failure: first day of ART cessation lasting ≥ 14 days, self-report | Intent-to-treat | Kaplan-Meier curves and Log-rank test |
| Cumulative ART use time | Continuous: number of weeks ART used in 12 months, self-report | Intent-to-treat | Wilcoxon rank-sum test |
| **Development of drug resistance** | | | |
| Antiretroviral drug resistance | Binary: presence of IAS-defined drug resistance mutations (during 12-month intervention phase) that were not present in baseline sample or in resistance test conducted prior to study (if available) | Intent-to-treat, missing values excluded | Chi-square test |
| **Substance abuse treatment outcomes** | | | |
| Retention to substance abuse treatment | Time to failure: discontinuation from opioid-treatment program | Intent-to-treat | Kaplan-Meier with log-rank test; Cox proportional hazards model adjusting for prior time in methadone program |
| Active drug use | Continuous: proportion of total available drug screens positive for opiates or cocaine. [Protocol-driven and clinical drug screens (required monthly by law in methadone clinics)] | Intent-to-treat, missing excluded, censored at methadone discontinuation | Wilcoxon rank-sum; Poisson regression with count of positive screens per follow-up months excluding periods with no testing |

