We will carry out a primary unadjusted analysis comparing study endpoints in the DAART and SAT arms. Two-sided P values < 0.05 will be considered to be statistically significant. The primary endpoint for this study will be suppression of the viral load below 50 c/ml evaluated at the 3 follow-up visits during the active intervention period (3, 6 and 12 months). Statistical generalized linear models for repeated observations will be used with the generalized estimating equations (GEE) approach to account for intra-person correlation. An intent-to-treat rule will be used, with missing values excluded. An 18-month follow-up (6 months after DAART intervention concludes) will be performed as a secondary analysis to assess durability. A supplementary on-treatment analysis will also be conducted. Secondary, multivariate analyses will be used to adjust for differences in possible confounding variables that may arise despite randomization. Data collection for the study will include detailed demographic, clinical, and psychosocial factors that may be associated with study outcomes, including prior opportunistic conditions, hepatitis B and C, baseline CD4 count and HIV RNA level, prior treatment experience, and validated metrics of drug and alcohol abuse, depression, and quality of life. We will assess whether adjustment for potential confounders, using multivariate modelling techniques, affects study inferences.For the analysis of immune restoration, we will use an intention-to-treat approach, with last observation carried forward for missing data points. The mean change in CD4+ cell count from baseline will be compared in the study arms at the designated follow-up times. Alternatively, a survival analysis approach will be used with time until first CD4 increase >100 or counts >500 as the outcome and censoring at last visit for each person.

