**Statistical power**

In this analysis, we will use methods that can incorporate repeated measurements and account for possible intra-person correlations. Such methods include generalized linear models with generalized estimating equation (GEE) approach or random effects models that can handle binary as well as continuous outcomes. Thus, overall, the number of observations available for comparison of the experimental and control arms of the study will be increased and missing observations will be excluded only for the time points where values of the outcome are missing. Calculations of sample sizes are based on models for longitudinal data analysis (Diggle PJ, Heagerty P, Liang KY, Zeger SL. Analysis of Longitudinal Data. 2002 Oxford University Press, Publ.) are shown in the following table.

The table below shows the power to detect a range of deltas in the DAART arm according to different viral suppression rates in the SAT arm, assuming alpha=0.05, enrollment of 60 per study arm, an intra-subject correlation of 0.2, and 15% loss to follow-up over one year. The table demonstrates >80% to detect deltas >0.20 across varying assumptions.

| **Table. Study Power with sample size of 60 per arm.** | | | | |
| --- | --- | --- | --- | --- |
| **Proportion in control (P0)** | **Delta in DAART arm (P1-P0)** | | | |
|  | **0.15** | **0.18** | **0.20** | **0.25** |
| 0.25 | 0.659 | 0.804 | **0.875** | **0.969** |
| 0.30 | 0.628 | 0.778 | **0.854** | **0.962** |
| 0.35 | 0.609 | 0.762 | **0.842** | **0.958** |
| 0.40 | 0.599 | 0.756 | **0.838** | **0.958** |

|  |  | | |
| --- | --- | --- | --- |
|  |  |  |
|  |  |  |  |
|  |  |  |  |
|  |  |  |  |
|  |  |  |  |
|  |  |  |  |
|  |  |  |  |
|  |  |  |  |
|  |  |  |  |
|  |  |  |  |
|  |  |  |  |

Differences of 15% to 20% in viral suppression rates are frequently considered to be evidence of therapeutic superiority in clinical trials comparing antiretroviral regimens. The detectable difference afforded by our sample size is conservative compared to the differences that we estimated in our pilot study. At 6 months and 12 months the absolute differences in viral suppression between DAART and the methadone maintained group who were self-administering HAART were +30 and +23, respectively.

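### Carrying the last CD4 count forward does not fit the plan's general rule for missing visits and can mix retention into the CD4 comparison; the alternative event of a count above 500 has no baseline condition

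*Protocol*

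**What the plan says.** The statistical plan under Study Statistics covers CD4 (immune restoration) in three sentences. The first sets the missing-data rule: "we will use an intention-to-treat approach, with last observation carried forward for missing data points". The second compares mean change from baseline between arms at the follow-up visits. The third offers a survival analysis as an alternative, with "time until first CD4 increase >100 or counts >500 as the outcome" and censoring at each person's last visit.

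Three other places bear on this.

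- **Same section, primary viral-load endpoint:** "An intent-to-treat rule will be used, with missing values excluded".
- **Statistical power:** the methods are described as a "generalized estimating equation (GEE) approach or random effects models that can handle binary as well as continuous outcomes", and the section goes on to say that "missing observations will be excluded only for the time points where values of the outcome are missing".
- **Table of secondary outcomes:** change in CD4 is compared at 3, 6 and 12 months by ANOVA at each visit and by linear regression with GEE overall. A separate row for the CD4 count gives "Linear regression with GEE & adjusting for initial CD4 at baseline". Both CD4 rows are marked intent-to-treat and give no missing-data rule. The row for change in HIV RNA, the other continuous laboratory outcome, leaves missing values out.

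**The concern.** A carried value is not a 12-month measurement. If CD4 rises through the year, a participant last seen at month 3 is frozen at an early, lower gain. When more people leave one arm, that arm's 12-month mean is pulled down even if recovery on therapy is identical.

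Unequal loss is a realistic possibility in this trial. The protocol compares retention on ART and in the opioid treatment program as outcomes and lists better retention on ART among the probable benefits. Only DAART brings frequent contact with site managers. Participants still at the clinic get spoken and written visit reminders, while those who have left must be traced. Twelve-month methadone retention runs from 70% to 90% across the sites.

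The alternative event raises a separate problem. Its above-500 limb does not look at where the participant started, so it can record recovery in someone who has not changed.

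At stake is whether a CD4 difference can be read as immune recovery, and whether two analysts following this protocol would run the same analysis.

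**Working it through.** **1. The plan's own figures.** The protocol gives no power or effect size for CD4. Its only loss figure is 15% over one year, in the power table for viral suppression. That table reproduces with an effective number per arm of 60 × 0.85 × 3 / (1 + 2 × 0.2) = 109.3 and a pooled two-proportion test. For a control rate of 0.25 and a delta of 0.20 this gives 0.878 against the printed 0.875, and all 16 cells agree within 0.0075. So 15% loss and three visits are the real planning inputs. This does not test the CD4 rule.

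**2. Effect of carrying values forward.** Inputs that are assumptions: the same true mean change in both arms (c3, c6, c12 at months 3, 6 and 12), permanent drop-out unrelated to CD4, and baseline carried forward (change 0) for anyone lost before month 3. With d3, d6, d12 the cumulative shares lost by each visit, the expected 12-month mean is

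(1 − d12)·c12 + (d12 − d6)·c6 + (d6 − d3)·c3 + d3·0.

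For a trajectory of 50/80/120 cells:

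- 15% lost in each arm (5/10/15%): 0.85×120 + 0.05×80 + 0.05×50 = 108.5 in both; difference 0.
- 10% lost (3/7/10%): 0.90×120 + 0.03×80 + 0.04×50 = 112.4. 20% lost (7/13/20%): 0.80×120 + 0.07×80 + 0.06×50 = 104.6. Difference 7.8.
- 5% lost (2/3/5%): 0.95×120 + 0.02×80 + 0.01×50 = 116.1. 25% lost (8/17/25%): 0.75×120 + 0.08×80 + 0.09×50 = 100.9. Difference 15.2.

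Both unequal pairs average the planned 15%. Across trajectories:

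| True change at 3/6/12 months | 15% vs 15% | 10% vs 20% | 5% vs 25% |
| --- | --- | --- | --- |
| 40/60/100 | 0 | 6.8 | 13.2 |
| 50/80/120 | 0 | 7.8 | 15.2 |
| 60/100/150 | 0 | 9.8 | 19.2 |

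With missing visits left out, the expected difference is 0 in every cell, because drop-out is assumed unrelated to CD4.

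**3. Against the noise.** With 60 per arm, SE = SD × √(2/60), which is 18.3 cells for an assumed SD of 100 and 27.4 for 150. The two-sided false-positive rate is Φ(−1.96 + δ/SE) + Φ(−1.96 − δ/SE). For δ = 7.8 and SD 100, δ/SE = 0.43 and the rate is 7.1%. Over the whole grid it is 5.7% to 8.4% for 10% versus 20% loss, and 7.7% to 18.3% for 5% versus 25%, against a nominal 5%.

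**4. The above-500 limb.** Under Inclusion criteria, item 5 is met by prior ART alone. The CD4 threshold there is a nadir and only one of several options. The threshold on a current laboratory value is for HIV RNA, so nothing keeps out a participant whose current CD4 exceeds 500. Take a true count of 550 that never changes, with an assumed SD of 60 to 100 for each measurement. The chance of exceeding 500 at month 3 is Φ(50/SD): 0.80 for SD 60 and 0.69 for SD 100. The chance of an apparent rise above 100 is 1 − Φ(100/(SD√2)): 0.12 and 0.24. The above-500 limb is therefore what makes this participant a likely event.

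**The case against.** The best defence is that the protocol sets missing-data rules outcome by outcome. The sentence that leaves missing values out, in the statistical plan, belongs to the primary viral-load endpoint. The sentence in Statistical power explains why repeated measures add observations, ahead of a viral-suppression table, and says what the methods can handle. The silence of the CD4 rows is compatible with a separate CD4 rule in the text. This stands in part: a reader might infer a flat contradiction, and the wording does not support that. What remains is an inconsistency with a general statement that names continuous outcomes, and a rule that the planned GEE models do not need.

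A reader might also infer that 60 values where 51 were observed make the standard error about 8% too small, from √(51/60) = 0.92. That does not follow. Each participant contributes one value, the 60 values are independent, and their sample variance correctly gives the sampling error of the mean last-observed change. The fault is that this mean is the wrong target.

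A third tempting reading is that DAART will be favoured. The protocol gives no loss by arm. With equal loss of the same timing the distortion is zero, and it changes sign if more DAART participants are lost. If leavers stop therapy and their counts fall, the direction may also differ.

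On the above-500 limb, it is fair to say that such an entrant is a likely event rather than a certain one, that the number of such entrants is not stated, and that randomisation balances them in expectation. The effect is therefore mainly dilution, in an alternative analysis of a secondary outcome. The at-risk set could be left to an analysis plan, but the event definition stands in the protocol and is incomplete as written.

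**Conclusion.** The point holds in a limited form. The CD4 missing-data rule is inconsistent with the general statement in Statistical power and is unnecessary for the models in the outcome table. It can produce a CD4 difference where true recovery is equal: 6.8 to 9.8 cells at 12 months with 10% versus 20% loss, 13.2 to 19.2 with 5% versus 25%, and none with equal loss. At the planned 15% overall loss the distortion is modest unless the arms differ sharply. These sizes rest on assumed trajectories, SDs and loss by arm, none of which the protocol supplies. Separately, the above-500 limb can count participants as recovered without a gain, and its weight depends on an unknown number of entrants above 500. Only a secondary outcome is affected, but the wording should be corrected.

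**What to change.** - Make one baseline-adjusted repeated-measures model on the observed 3-, 6- and 12-month CD4 values the main CD4 analysis, fitted by GEE or as a mixed model. Keep last observation carried forward only as a sensitivity analysis. State the rule on the CD4 rows as well as in the text.
- Apply the above-500 criterion only to participants at or below 500 at baseline; require the increase of more than 100 for the others.
- Call the time-to-event analysis supportive, so that it is clear which analysis carries the CD4 conclusion.

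The cost is mostly wording. GEE regression is already on the CD4 rows, although the baseline adjustment and the three visits stand on separate rows. The table names no mixed model, but Statistical power allows random effects models. Each visit has slightly fewer values: with 15% loss, 60 × 0.85 = 51 per arm at 12 months. The change reduces the drop-out problem without removing it. GEE on observed visits still assumes missingness unrelated to outcome, and a mixed model needs a weaker assumption, which is a reason to prefer it.

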Inclusion criterion number 4 is designed to assure equal access to therapy at study enrollment. ART will not be provided as part of this study. Coverage for ART will be addressed through patients’ primary care clinics. In our study population, antiretroviral therapy coverage is generally obtained through Medicaid or the Maryland AIDS Drug Assistance Program (MADAP). Our site managers will assist individuals in accessing appropriate resources, but participants will not be enrolled until medication coverage and receipt of prescriptions from a medical provider has been verified. Exclusion criterion 3 is designed to exclude individuals with such extensive drug resistance that viral suppression is unlikely, even with high-level adherence. A summary resistance profile will be compiled that assumes that any resistance mutation or phenotypic drug resistance documented in the past is never lost. The cumulative mutation list will be entered into the Stanford University web-based HIV drug resistance database ([http://hivdb.stanford.edu](http://hivdb.stanford.edu/)) for analysis. Drugs in the proposed regimen will be considered to be fully active (i.e., score=1.0) if categorized as “susceptible” or “potential low-level resistance”, and to be partially active (i.e., score=0.5) if categorized as “low-level resistance” by the Stanford database. Drugs in the proposed regimen with “intermediate“ or “high-level” resistance will not be assumed to have any antiviral activity. Results from phenotypic resistance tests (if available) will be incorporated into the assessment individual drug activity. Enfuvirtide (fusion inhibitor) and raltegravir (integrase inhibitor) will be assumed to be fully active if they have not been used previously. CCR-5 inhibitors (e.g., maraviroc) will be assumed to be fully active if an agent in this drug class has not been used previously and a tropism assay performed within the previous 4 weeks shows exclusively R5-tropic virus. Scores form each drug in the proposed regimen will be summed for a “regimen activity score.” To be eligible for the study a participant’s “regimen activity score” must be greater than or equal to 1.5.

Enrollment and randomization

120 participants will be enrolled to assess the outcomes of this study.

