Clinical specimens (blood and urine samples) will be obtained by the study coordinator at assessment visits. In addition to the unique identification number, clinical specimens will be further identified by a two digit visit code, a one digit code for specimen type, and a one digit code identifying the specimen aliquot for banked plasma. Specimens will be transported back to Johns Hopkins in designated transport containers and processed the same day. Laboratory tests, including CD4 cell count and HIV RNA will be performed in real time, and test results will be sent to participants’ medical providers. Plasma for resistance tests will be processed and stored at -50 C for drug resistance testing. Paired resistance testing will be performed on the baseline sample and the last available sample in which the HIV RNA level was above 500 c/ml and the participant was taking antiretroviral therapy. Results of urine toxicology screens will be masked until the conclusion of the study, and then will only be available to study personnel conducting analyses. Results of the urine toxicology screens will not be made available at any time to medical providers, methadone clinic staff, or others without signed permission from the participant.

The questionnaire component of the assessment visits will be administered by the study coordinator by face-to-face interview at study assessment visits. The study coordinator will read questions to participants in a private office and record results directly onto a computer tablet using a Microsoft-Access-based data entry template.

Measurement methods, assays, and instruments

| **Factor assessed** | **Assay or instrument** |
| --- | --- |
| HIV-1 RNA | Amplicor 1.5 (Roche Diagnostics) |
| CD4+ cell count | Flow cytometry – Johns Hopkins Clinical Laboratory |
| Antiretroviral resistance | HIV-1 protease and reverse transcriptase genotyping (Quest Diagnostics, Baltimore, MD) |
| Substance use | Urine immunoassay for amphetamines, barbiturates, benzodiazepines, cocaine, opiates, cannabinoids, and phencyclidine (Friends Medical Laboratory, Inc., a CLIA-approved facility [http://www.friendslab.com](http://www.friendslab.com/)) |
| Self-reported drug and alcohol use | ACASI-based survey – modified questions from the Addiction Severity Index (ASI); AUDIT survey for at-risk alcohol use. |
| Self-reported adherence | ACASI-based survey – 4 questions. |
| Depression/anxiety | ACASI-based survey – Hospital anxiety and depression scale (HADS) |

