The development of new antiretroviral drug resistance will be compared in the DAART and SAT arms. Genotypic antiretroviral resistance testing will be performed on the last available plasma sample from (3, 6, 12, or 18 months) when the HIV RNA > 500 c/ml and the subject remains on antiretroviral therapy. Stored plasma from baseline will be run simultaneously to determine if new resistance mutations have developed. Antiretroviral resistance testing is generally not possible at viral loads below 500 c/ml to 1,000 c/ml. Drug resistance mutations will be interpreted according to the classification system of the International AIDS Society – USA [3]. Development of antiretroviral resistance will be defined as the presence of  1 major resistance mutation in the protease or reverse transcriptase genes during study follow-up that was not present at baseline. Subjects with HIV RNA levels < 500 c/ml at all follow-up time points will be considered to have not developed drug resistance. Participants who are lost to follow-up, or who have HIV RNA levels > 500 c/ml, but in whom genotypic antiretroviral resistance testing is not technically feasible, will be omitted from the analysis. Exploratory analyses are planned on treatment-naïve and –experienced subgroups, and on differences in the development of protease inhibitor-, non-nucleoside reverse transcriptase inhibitor-, and nucleoside reverse transcriptase inhibitor-associated resistance mutations.

Retention to opiate agonist therapy will be compared in the DAART and SAT arms using survival analysis techniques. Follow-up time will be modeled from the date participants initiated opiate agonist therapy (origin), with subjects coming under observation at study enrollment, to account for delayed entry and potential lead time bias. Subjects will be considered to have failed when they discontinue or are discharged from methadone maintenance therapy. We will also compare the proportion of participants with active substance abuse at baseline and during the study in the DAART and SAT groups. Active substance abuse will be defined as having a urine toxicology screen positive for drugs of abuse or self-reported (ACASI) illicit drug use, or at-risk alcohol use in the 3 months preceding the survey assessment. Logistic regression with generalized estimating equations, will be used to compare the longitudinal risk of active substance abuse in the study groups, with standard errors adjusted for repeated observations.

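### The drug-resistance endpoint has two incompatible definitions, and with one follow-up genotype per person the 12-month version cannot be derived for some participants

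*Protocol*

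**What the plan says.** Two parts of the protocol's Study Statistics section define new resistance.

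- **Secondary outcome variables table, drug resistance row:** "Binary: presence of IAS-defined drug resistance mutations (during 12-month intervention phase) that were not present in baseline sample", or in a pre-study resistance test where one exists. The comparison is a chi-square test.
- **Statistical plan, resistance paragraph:** genotyping "will be performed on the last available plasma sample from (3, 6, 12, or 18 months"). To qualify, a sample must be viraemic above 500 c/ml and come from someone still taking treatment. An event is at least one major "resistance mutation in the protease or reverse transcriptase genes during study follow-up that was not present at baseline". A participant counts as free of resistance only if HIV RNA is below 500 c/ml at every follow-up time point. Those lost to follow-up, or viraemic but not testable, are omitted.

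The Assessment visits section repeats the selection rule without a month limit: "Paired resistance testing will be performed on the baseline sample and the last available sample" that was viraemic on therapy. The Human Biological Samples section explains that plasma is stored so that only the sample most likely to show new resistance need be tested, to contain cost. The Study Summary ends directly administered therapy at 12 months and follow-up at 18.

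**The concern.** The two definitions differ in three respects: the time window, the comparator for calling a mutation new, and the class of mutation counted. The same patients can yield different event counts depending on which one is followed.

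The window matters most because it is built into a laboratory step. If the month-18 sample is the one genotyped, an analyst cannot later recover the 12-month state from the data. After month 12 both arms self-administer, so a mutation found at month 18 may have arisen after the randomised difference in treatment ended. The primary endpoint (months 3, 6 and 12) and the CD4 change row (same visits) keep to the intervention period. The resistance paragraph does not, although the table says it should.

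**Working it through.** The protocol gives no rate, power or sample size for this endpoint, so there is no stated figure to reproduce. The core of the check is a comparison of the texts.

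**The two definitions side by side**

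| Element | Secondary outcomes table | Statistical plan |
|---|---|---|
| Window | 12-month intervention phase | study follow-up; samples to month 18 |
| Comparator | baseline and any available pre-study test | baseline only |
| Mutation class | IAS-defined | at least one major, by the IAS-USA classification |

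**What one follow-up genotype can show**

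1. Last qualifying sample at month 3, 6 or 12: any mutation found falls within the 12-month window, so the table's endpoint can be derived.
2. Viraemic on therapy at month 18: that sample is the only follow-up genotype. A new mutation in it could have arisen before or after month 12.
3. Below 500 c/ml through month 12, then viraemic on therapy at month 18: read over 12 months, this participant has no resistance. Under the statistical plan the participant is genotyped and may count as an event, or is omitted if testing fails.
4. Seen at month 12 but not at month 18: the rule omitting those lost to follow-up names no window, so a participant with a known 12-month outcome could be dropped.

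**How many participants could be in case 2 or 3 (illustration)**

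Inputs from the Statistical power section: 60 per arm and 15% loss over one year. Remaining per arm: 60 x 0.85 = 51. Assumed share viraemic on therapy at month 18: 20% to 60%. Then 51 x 0.20 = 10.2 and 51 x 0.60 = 30.6, or about 10 to 31 per arm with only a month-18 genotype. This ignores any loss between months 12 and 18.

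**What an 18-month window could do to the contrast (illustration)**

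Assumed: 12-month risk r of 10% with directly administered and 20% with self-administered therapy, then the same further risk h in both arms among those still free of resistance. Formula: 18-month risk = 1 - (1 - r)(1 - h).

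| h | Directly administered | Self-administered | Risk ratio | Risk difference |
|---|---|---|---|---|
| 0 | 10.0% | 20.0% | 0.50 | 10.0 points |
| 0.05 | 1 - 0.90 x 0.95 = 14.5% | 1 - 0.80 x 0.95 = 24.0% | 0.60 | 9.5 points |
| 0.10 | 1 - 0.90 x 0.90 = 19.0% | 1 - 0.80 x 0.90 = 28.0% | 0.68 | 9.0 points |

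With 51 per arm, power under these rates is about 29% for the 12-month window and 23% to 19% for the 18-month window.

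**Events given up by a 12-month window, same assumptions**

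Summed risks: 10 + 20 = 30 at 12 months, against 14.5 + 24 = 38.5 or 19 + 28 = 47 at 18 months. Reduction: 1 - 30/38.5 = 22%, or 1 - 30/47 = 36%.

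**The case against.** The window conflict cannot be argued away, but several objections limit what follows from it.

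- **A reader might infer that an 18-month comparison is biased.** It is not. Participants stay in their randomised arms, so the intent-to-treat comparison remains valid. It estimates the effect of 12 months of directly administered therapy followed by self-administration. Dilution follows only if later resistance arises about equally in both arms, which the protocol neither states nor supports. Even then the risk difference barely moves, and the planned chi-square test names no risk ratio.
- **A reader might infer that the baseline-only comparator breaks the protocol's rule that "assumes that any resistance mutation or phenotypic drug resistance documented in the past is never lost".** That rule builds the resistance profile for eligibility and does not define this endpoint. The documents support only that the table excludes mutations seen in pre-study tests and the statistical plan omits that clause.
- **A reader might infer that the 12-month endpoint is lost for good.** The problem touches only participants viraemic on therapy at month 18. Plasma is stored, so an earlier sample can still be genotyped if the rule is changed before testing.
- **The single late sample is deliberate.** Cost and yield are stated reasons, and another secondary outcome, change in log HIV RNA, is compared through month 18. This would justify an 18-month endpoint if the protocol consistently named one; the outcomes table does not.
- **Weight.** This is one secondary endpoint, and under the assumed rates the comparison has low power with either window.

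These points reduce the likely consequences. None reconciles the two definitions.

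**Conclusion.** The concern holds as an inconsistency with a practical consequence. The protocol gives two incompatible definitions of one named outcome, and its sampling rule serves the 18-month one. Following it leaves the 12-month endpoint underivable where a new mutation is found in a participant viraemic on therapy at month 18. If that participant was below 500 c/ml through month 12, the two definitions can give opposite classifications.

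This conclusion rests on the text alone. The numerical illustrations rest entirely on assumed resistance and viraemia rates and an assumed equal later risk; the true size and direction of any change are unknown. The matter should be settled before stored plasma is genotyped, but it does not threaten the trial's main conclusion.

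**What to change.** 1. In Assessment visits and in the statistical plan, state that for the arm comparison the follow-up genotype is taken from the last on-therapy sample with HIV RNA above 500 c/ml at or before month 12.
2. Apply the rule for classing participants as free of resistance, and the rule omitting those lost to follow-up, to months 3, 6 and 12 only. Otherwise someone suppressed through month 12 and viraemic at month 18 would be left unclassified.
3. Use one definition of a new mutation in both places: the same mutation class, absent from baseline and from any available pre-study test, as the table already says for the comparator.
4. Report month 18 as a separate durability analysis only if a second follow-up genotype is affordable.

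**Cost.** Items 1 to 3 are wording changes and still need at most one follow-up genotype per person for the main comparison. The real downside is fewer events than with an 18-month window, about 22-36% fewer under the assumed rates. Item 4 needs an extra genotype for anyone with a qualifying sample both by month 12 and at month 18, which bears on the cost limit that the protocol set for itself.
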